## Abstract

**Supplementary Information:**

The online version contains supplementary material available at 10.1007/s11357-025-01511-1.

## Introduction

By 2050, one in every six individuals worldwide will be over 65 years old, leading to an increasing number of older adults globally relative to adults in the workforce [1]. Asia’s population is ageing faster than that of any other world region [2]. In Singapore, where the rate of ageing is particularly accelerated, 24% of the population is expected to be older than 65 years by 2030 [3]. Although governmental initiatives have been implemented to develop care solutions for older individuals [4] and to enable residents in Singapore to practise healthier lifestyle habits (e.g., the National Steps Challenge [5] and Nutri-Grade labelling [6]), the healthspan-lifespan gap is around 10 years, indicating that individuals have to endure a significant period of poor health that also stresses healthcare systems [7]. Thus, physiological and physical characterisation of the adult population is important to inform healthcare policies to guide early interventions.

Biological ageing is the primary driver of age-associated chronic diseases [8]. Higher biological age relative to one’s chronological age is characterised by reduced or impaired function of multiple organs required for the function of many physiological systems, such as the cardiovascular, metabolic, and musculoskeletal systems [9]. Differences in the rate of biological ageing can already be detectable at midlife [10]. Measuring biomarkers of ageing (molecular, physiological, and digital) will enhance understanding of the biological processes underlying ageing and their consequences [9]. Age-related changes can be observed at the (i) molecular and cellular levels, such as through DNA methylation patterns (molecular), with (ii) clinical assessments, such as for cardiovascular and physical functions (physiological), and by using (iii) digital devices, such as measuring physical activity and facial age (digital) [9].

Most knowledge about age-related changes has come from clinical studies conducted in Caucasian populations [11, 12]. However, genetic and lifestyle differences between Asian and Caucasian populations are associated with variations in biological age and health risk factors [13–16]. These differences have prompted further investigation into the physiological processes underlying ageing and its consequences in Asian populations [17–19]. Despite this need, a significant gap remains in the availability of relevant datasets for Asian populations. Singapore’s unique multi-ethnic population includes individuals of Chinese, Malay, and Indian ethnicities, and thus provides a valuable study resource to better understand the phenotypes associated with ageing in Asian populations [20].

The Ageing BIOmarker Study in Singaporeans (ABIOS) aims to describe molecular, physiological, and digital biomarkers of ageing in Singaporeans. The secondary aim is to explore factors (e.g., ethnicity, lifestyle, etc.) that are associated with these biomarkers of ageing.

## Methods

### Study design and setting

The Ageing BIOmarker Study in Singaporeans (ABIOS) is a single-centre observational and cross-sectional study of community-dwelling Chinese, Malay, and Indian adults conducted at Alexandra Hospital (AH, Singapore). Participants were recruited from the general Singapore population through diverse outreach efforts to ensure representation across ethnic minorities and age groups. These efforts include study advertisements distributed to the public, targeted outreach to various employers and occupational groups, and language-specific recruitment drives conducted in places of worship, religious organizations, and community associations throughout Singapore.

This study was approved by the National Healthcare Group Domain-Specific Review Board (NHG DSRB Ref: 2019–00388) with all ethical guidelines adhered to under the Declaration of Helsinki [21]. This study has been registered in ClinicalTrials.gov with the identifier NCT06555978. Written informed consent is conducted with all participants before the first study visit commences.

### Participant criteria and sample size

Eligible participants (up to *N* = 420) are community-dwelling adults aged 21 years and older, of Chinese, Malay, or Indian ethnicity, who have lived in Singapore for at least five consecutive years, and recruited between March 12, 2021, and July 1, 2024. Participants must be apparently healthy, non-smokers, and have no more than one health condition if ≥ 45 but < 65 years and can have more than one health conditions if ≥ 65 years. Participants must have all health conditions controlled by medication, if present, to be eligible. Detailed inclusion and exclusion criteria are outlined in Table 1.

**Table 1 Tab1:** Inclusion and exclusion criteria

Inclusion criteria	Exclusion criteria
≥ 21 years of age	Body mass index (BMI) ≥ 30 kg/m^2^
Chinese, Malay, or Indian and has lived in Singapore for at least 5 consecutive years	Pre-existing or history of major cardiovascular disease (e.g., coronary artery disease, heart failure, stroke, peripheral vascular disease)
Apparently healthy and non-smokers	Any metal implants (excluding dental implants) in the body
If ≥ 45 but < 65 years, having only 1 condition and it must be medication-controlled (if any): • Hypertension • Hyperlipidemia • Hyperglycemia • Osteopenia/osteoporosis • Osteoarthritis • Type 2 diabetes	Pre-existing or history of cancer or chronic obstructive pulmonary disease (COPD)
If ≥ 65 years, having any condition and they must be medication-controlled (if any): • Hypertension • Hyperlipidemia • Hyperglycemia • Osteopenia/osteoporosis • Osteoarthritis • Type 2 diabetes	Females currently pregnant or planning pregnancy in the next 6–12 months

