### Statistical analyses

The proposed analyses will involve several statistical methods. Participants’ characteristics will be analysed according to age as both continuous variables and categorical variables (e.g., young, 21–44 years; middle-aged, 45–64 years; and older, 65 years and above). Subgroup analysis will be conducted based on sex, ethnicity (Chinese, Malay, or Indian), and physical activity status. Descriptive analyses will be performed with the *t*-test, analysis of variance, Mann–Whitney *U* test, Kruskal–Wallis test, Chi-square test, and Fisher’s exact test. Data that are not normally distributed will be considered for log-transformation if applicable. For continuous outcomes, linear regression models will be constructed to compute mean difference and 95% confidence intervals (CI). Binary logistic regression models will be constructed to compute odds ratios and 95% CI for results with binary outcomes. Data will be analysed by statistical analysis software (RStudio, Stata and SPSS). All statistical tests will be conducted at 5% level of significance. The associations between molecular (e.g., DNA methylation age, metabolic and inflammatory biomarkers in blood, saliva, and stool), physiological (e.g., body composition, physical performance, arterial stiffness, skin autofluorescence, cognitive status), and digital (e.g., facial age, objectively measured physical activity) biomarkers will be investigated both within and between groups (young, 21–44 years old; middle-aged, 45–64 years; and older, 65 years and above; male and female; Chinese, Malay, and Indian).

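### The entry health rule loosens at 65, and by implication at 45, which are the cut-points of the planned age groups, so age-group contrasts partly reflect who was admitted

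*Protocol article*

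**What the plan says.** Under Participant criteria and sample size, the protocol article sets a health rule that depends on age:

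- **All ages:** Table 1 requires "Apparently healthy and non-smokers". Below 45 nothing more is said about the listed conditions.
- **45 to under 65:** "Participants must be apparently healthy, non-smokers, and have no more than one health condition if" in this age band. Table 1 lists six: hypertension, hyperlipidemia, hyperglycemia, osteopenia/osteoporosis, osteoarthritis and type 2 diabetes.
- **65 and over:** participants "can have more than one health conditions if" in this band, from the same list.
- **Treatment:** "Participants must have all health conditions controlled by medication, if present, to be eligible".

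Under Statistical analyses, participants' "characteristics will be analysed according to age as both continuous variables and categorical variables", with the groups given as "young, 21–44 years; middle-aged, 45–64 years; and older, 65 years and above". Associations between biomarkers are to be examined within and between these groups. The subgroup factors named are sex, ethnicity and physical activity status.

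**The concern.** The ages at which the entry rule changes are the ages at which the analysis groups change. A difference between neighbouring groups can therefore come from age, from the change in permitted disease, or from the change in permitted medication, which the treatment requirement makes step up at the same ages.

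The listed conditions bear directly on what is measured: blood pressure and arterial stiffness, lipids, glucose, insulin and HbA1c, bone density, and physical performance. The primary aim is to describe biomarkers of ageing. A step at 65 that arises partly from admission could be reported as an ageing phenotype, and the Discussion does not raise this possibility.

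**Working it through.** **1. The cut-points side by side**

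| Age group analysed | Listed conditions permitted at entry |
|---|---|
| 21–44 | none named (implied, not stated) |
| 45–64 | 0 or 1, medication-controlled |
| 65 and above | any number, medication-controlled |

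The change at 65 is explicit. The change at 45 is an inference from the list starting at that age.

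**2. What adjustment can and cannot do.** On this reading, zero conditions can occur in all three groups, exactly one in the two older groups, and two or more only at 65 and above. A model with age and condition count has no data below 65 at counts of two or more. Its separation of age from multimorbidity there rests on the assumed form of the model. Only the zero-condition stratum is shared by all three groups.

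**3. Size.** The article gives no figure to reproduce: up to 420 participants, with no age split, SD or effect size. What follows is an illustration.

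Assumptions, none from the documents: the underlying number of conditions is Poisson with mean λ; none are admitted under 45; each condition shifts a marker by 0.3 SD. The mean count is then λ under open entry. Under the entry rule it is 0 (under 45), λ/(1+λ) (45–64) and λ (65 and above).

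*Group contrasts in mean condition count, rule versus open entry:*

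| Assumed λ (young / middle / older) | Contrast | Rule | Open | Excess | × 0.3 SD |
|---|---|---|---|---|---|
| 0.1 / 0.5 / 1.0 | middle–older | 0.67 | 0.5 | 0.17 | 0.05 |
| | young–older | 1.0 | 0.9 | 0.1 | 0.03 |
| | young–middle | 0.33 | 0.4 | −0.07 | −0.02 |
| 0.3 / 1.0 / 1.8 | middle–older | 1.3 | 0.8 | 0.5 | 0.15 |
| | young–older | 1.8 | 1.5 | 0.3 | 0.09 |
| | young–middle | 0.5 | 0.7 | −0.2 | −0.06 |

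The excess is largest at the 65 boundary. The young–middle gap narrows slightly.

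*Local step at a cut-point, with the same λ on both sides:* at 65 it is λ − λ/(1+λ), which is 0.36 conditions at λ = 0.8 and 1.16 at λ = 1.8. At 45 it is λ/(1+λ), which is 0.17 at λ = 0.2 and 0.44 at λ = 0.8. These steps stay in the data when age enters as a continuous variable.

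**4. Precision.** Assuming 140 per group (equal thirds of 420) and SD 1, the standard error of a two-group difference is √(2/140) = 0.1195 SD. An excess of 0.15 SD alone would be declared significant about 24% of the time at two-sided 5%, and 0.09 SD about 12%.

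If half of the older group has no listed condition, the older–young standard error becomes √(1/140 + 1/70) = 0.146 SD. The ratio 0.146/0.1195 is 1.22, about 22% larger.

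**The case against.** **Disease rises with age anyway.** This stands and limits the size. A reader might multiply the whole older–young difference in conditions by the effect per condition, for example 1.2 × 0.3 = 0.36 SD. With 140 per group that would be significant about 85% of the time (0.36/0.1195 = 3.01), and the reader might call all of it an artefact of the design. The documents do not support that. Most of that difference would also be present under open entry, and only the excess belongs to the rule. The group size of 140 is itself an assumption.

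**The two boundaries are not alike.** This also stands. The rule under 45 is only implied, and relative to open entry the young–middle gap shrinks slightly.

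**The aim is descriptive.** The Introduction presents biological ageing as a driver of chronic disease, so conditions are partly a consequence of ageing and not simply a contaminant. This is a good reason not to make a condition-free set the main analysis. It does not rescue the full-sample contrast, because a description of age groups still depends on each being admitted by a comparable rule.

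**Covariates may be set out elsewhere.** A condensed article need not list them, and their absence is no part of this point. The non-overlap is fixed by eligibility, which is stated here, and a covariate list cannot undo it.

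**Fixed exclusions may pull the other way.** Excluding cardiovascular disease, cancer and COPD at all ages may make older participants healthier and shrink age differences. The documents give nothing from which to net this off.

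**Conclusion.** The point holds as a limit on design and interpretation. No stated number is wrong and no passages contradict each other. The match between the entry rule and the age groups is exact at 65 and implied at 45, so age-group contrasts, chiefly 45–64 versus 65 and above, partly reflect the entry rule.

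The size is not known. At 0.3 SD per condition and the assumed morbidity, the rule's excess over open entry is roughly 0.05 to 0.15 SD for middle-aged versus older and 0.03 to 0.09 SD for young versus older. It scales directly with the effect per condition, which will differ between markers and may change sign where medication acts on the marker.

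A reader might infer that age findings from this study are mainly products of selection. The documents do not show that. They show that the full sample alone cannot distinguish a step at 65 due to age from one due to admission.

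**What to change.** Recruitment ended on July 1, 2024, so the change lies in analysis and reporting:

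1. Keep the full-sample age analysis, grouped and continuous.
2. Pre-specify beside it the same age contrasts restricted to participants with none of the six listed conditions, at every age.
3. State that full-sample contrasts compare groups admitted under different health rules, and that a step at 45 or 65 that is absent in the restricted set will not be reported as an ageing phenotype. Judge this by estimates and intervals, since the restricted set is smaller.
4. State which listed conditions, if any, were permitted under 45.

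The cost is some wording and one further run per outcome on data already collected. There are two downsides. Intervals involving the oldest group widen: the older–young standard error is about 22% larger if there are 140 per group and half of the older group is condition-free. The condition-free older group is also healthier than average for its age, and restricting to it conditions on a possible consequence of ageing. The restricted result is therefore a sensitivity analysis to be read with the full-sample result, not in place of it.

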### Screening

After indication of interest, individuals are screened over a phone call for eligibility (Table 1) to participate based on previous and current medical history. Individuals are excluded if they are unable or unwilling to provide written informed consent, without a legal proxy to consent, or are ineligible due to any of the exclusion criteria. If they are eligible according to the screening inclusion criteria, they will be invited for the study visits.

### Study visits

Eligible participants attend the two study visits at AH. Written informed consent is obtained from all participants prior to data collection. A pre-trial questionnaire is administered to check if the participants feel fit to perform the study assessments at the beginning of each visit. Resting blood pressure measurement on the right arm using a digital automated sphygmomanometer (Automatic Blood Pressure Monitor HEM-7121, Omron Healthcare) is taken to ensure it is ≤ 160/90 mmHg before commencing assessments. The two visits are conducted approximately 11 to 21 days apart (Fig. 1). During the first visit, anthropometry, bone density and body composition with dual energy X-ray absorptiometry (DEXA), assessments for skin autofluorescence, arterial stiffness, physical performance, and facial morphology image capture are conducted in addition to the health and lifestyle survey, physical activity questionnaire, cognitive performance test, and nutritional assessment (Table 2). Between the first and second visits, the participant is provided with a physical activity monitor, physical activity diary, and a dietary food record for remote data collection. The stool collection kit, along with instructions, is also provided to the participant. They return the physical activity monitor, physical activity diary, food record, and stool sample during their second visit. During the second visit, collection of blood and saliva is conducted (Table 2).

**Fig. 1 Fig1:**
[figure not shown]
Workflow of ABIOS study recruitment process and study design. Screening of interested individuals is conducted via phone call (*Screening*). Eligible participants complete informed consent before commencing the indicated assessments in the clinic during the first visit (*Clinic Visit 1*). They will then bring home an activity monitor, a 7-day physical activity diary, a 3-day dietary food record, and a stool collection kit for remote data collection (*At-Home Data Collection*). They will return to the clinic during the second visit for collection of blood and saliva and return of the activity monitor, activity diary, dietary food record, and the stool sample collected the morning of the visit (*Clinic Visit 2*). The first and second visits are conducted approximately 11 to 21 days apart

**Table 2 Tab2:** Overview of assessments and visits

Methodology	1st visit	Home*	2nd visit
Signed Informed Consent	**√**		
*Clinical assessments*			
Anthropometry	**√**		
Body Density and Body Composition (DEXA scan)	**√**		
Skin Autofluorescence (AGE reader)	**√**		
Arterial Stiffness (carotid-femoral pulse wave velocity)	**√**		
Physical Performance	**√**		
3D Facial Ageing image	√		
*Questionnaires & surveys*			
Health & Lifestyle Survey	√		
Modified Pittsburgh Sleep Quality Index questionnaire	√		
SATED questionnaire	√		
Global Physical Activity Questionnaire (GPAQ)	√		
Montréal Cognitive Assessment (MoCA)	√		
FRAIL	***√***		
Mini Nutritional Assessment (MNA)	√		
7-day Physical activity diary		√	
3-day Food record		√	
*Blood parameters*			
DNA methylation			√
Complete blood count			√
Fasting haematological panel			√
Fasting lipid profile			√
Fasting glucose			√
Fasting liver profile			√
Insulin & HbA1c			√
Immune and inflammatory markers			√
*Other samples and assessments*			
Saliva samples			√
Stool samples		√	
Activity monitor		√	

^*^Home indicates remote data collection at home

Abbreviations: *3D*, three-dimensional; *AGE*, advanced glycation end products; *DEXA*, dual-energy x-ray absorptiometry; *HbA1c*, haemoglobin A1c

Physical performance assessments include handgrip strength, 4-m walk, arm curl, chair sit to-stand, back scratch, and eight repetition-maximal leg extension assessments

To minimize dropout rates following the initial visit, several retention strategies were implemented. First, participants receive regular reminders (via WhatsApp or email) before each scheduled visit. Second, flexible scheduling options are offered to accommodate participants’ availability. Additionally, participants are provided with reimbursement vouchers to reduce logistical barriers to and increase incentives for attendance.

### Molecular biomarkers of ageing

#### DNA methylation

DNA will be extracted from de-identified peripheral blood mononuclear cell (PBMC) samples using QIAamp® DNA Mini Kits (QIAGEN Singapore Pte. Ltd.). The quality of the genomic DNA will be assessed using the Qubit™ fluorometer, through A260/A280 and A260/A230 spectrophotometry ratios and the concentrations of DNA isolated. Approximately 1 µg of genomic DNA from each participant will be bisulphite-treated using the Zymo EZ DNA Methylation Kit (Zymo Research Corporation) to convert non-methylated cytosine nucleotides to uracil for subsequent methylation profiling. The Illumina Infinium MethylationEPIC v2.0 BeadChip Kit (the “935 K”) (Illumina, Inc., USA) will be used for high-throughput genome-wide DNA methylation measurement. The 935 K enables reliable and reproducible evaluation of over 935,000 CpG methylation sites, offering extended genomic coverage of gene regulatory regions compared to its 850 K predecessor [22]. The biological age of participants will be analysed using blood-based DNA methylation clocks: Horvath [23], Hannum [24], PhenoAge [25], GrimAge [26], DunedinPoAM [27], and DunedinPACE [12]. The biological age of the participants will be analysed using each clock separately and using the mean biological age derived from the Horvath, Hannum, PhenoAge, and GrimAge clocks.

#### Blood, saliva, and stool parameters

Peripheral blood (up to 52 mL) will be drawn into Vacutainer plain tubes, EDTA tubes, or sodium fluoride tubes from the antecubital vein by a certified phlebotomist, with the participant having fasted overnight and in a seated position. Blood samples are analysed immediately according to well-established protocols for haematology, coagulation, and biochemistry test parameters: complete blood count, haematology panel, lipid panel, glucose, glycated haemoglobin (HbA1c), insulin, and liver protein panel (total bilirubin, aspartate transaminase, alanine transaminase, gamma-glutamyl transferase, total protein, albumin, globulin) (Supplementary Material, Table 1). PBMCs are isolated from whole blood immediately after blood collection using the Lymphoprep™ density gradient medium in SepMate™ PBMC isolation tubes (STEMCELL Technologies Inc., Canada) and cryopreserved in liquid nitrogen until future DNA methylation profiling and immunophenotypic analysis (Supplementary Material, Table 1). The remaining blood samples in the form of frozen buffy coats, plasma, and serum are stored at –80℃ for future analysis, including circulating immune and inflammatory markers (several myokines, cytokines, damage-associated proteins, metabolites as well as several inflammatory biomarkers) (Olink®, Uppsala, Sweden) (Supplementary Material, Table 1). Samples are placed on ice or in a 4℃ fridge until they can be processed, and the maximum time allowed from sample collection to processing is two hours.

Fasted saliva samples are collected from the participants, who are instructed to passively drool into a plastic funnel that is attached to the top of the saliva collection tube, which is pre-filled with guanidine-free, DNA stabilization buffer (Muhdo Health Ltd., Ipswich, UK). Samples are immediately placed on ice until they can be stored in –80℃ freezers. The samples are cryopreserved at –80℃ until future extraction of genomic DNA with the QIAamp® DNA Mini Kit (QIAGEN Singapore Pte. Ltd.) for subsequent metagenomics sequencing to analyse the salivary microbiome as oral microbial signatures were found to associate with age and frailty [28] (Supplementary Material, Table 1).

Stool samples for gut microbiota analyses are collected for metagenomics sequencing to estimate microbial richness and diversity. Participants are provided with an empty stool collection container during the first visit. The stool samples are collected within 24 h of the second visit (e.g., collected the night before and kept in the refrigerator or collected the morning of the second visit and not kept in the refrigerator) and returned in the stool container during the second visit to be stored at –80℃ for future analysis (Supplementary Material, Table 1).

